## Data analysis and criterion for assessing feasibility of trial

The progress of all eligible participants will be described, from screening to completion of the study, using a CONSORT flow diagram. Descriptive statistics for continuous variables (mean, interquartile ranges) and categorical variables (frequency counts, percentages) will be used to summarise baseline characteristics of screened and enrolled patients. Potential barriers to recruitment will be investigated by comparing the descriptive statistics between those recruited and those eligible but not recruited using chi-squared or Fisher’s exact tests for categorical data and Mann–Whitney U tests for continuous data. The proportion of participants who successfully complete consent, randomisation, receipt of intended treatment allocation, and evaluation for each objective will be described as percentages of the total number screened for eligibility and approached. The reasons given for not recruiting eligible patients will be collated and described. The proportion of enrolled patients remaining in their allocated treatment arm will be described as percentages of the total number randomised. The time taken for each stage of patient flow will be described as medians (with interquartile ranges) and graphically using Kaplan–Meier plots.

Qualitative interview data will be transcribed internally, checked, and anonymised as the study progresses. QSR NVivo software will be used to assist in the organisation and indexing of qualitative data. Data will be analysed thematically, and analysis will be informed by the constant comparison approach of grounded theory [22]. Both the interview topic guides and the parental surveys have been adapted from the framework of acceptability to facilitate a robust analysis to address acceptability outcomes [17]. Parent/guardian(s) will complete surveys prior to the additional interviews, and their responses will be available to the interviewer. This is designed for triangulation of survey responses; however, the interviews will be able to support the development of new ideas, particularly regarding ways to improve the study design, and may identify themes beyond the framework which may not have been identified by the researchers.

Thresholds to assess feasibility have been determined a priori by relevant outcomes used in randomised controlled trials for the management of preschool wheeze and existing literature for the design of feasibility studies [6, 18, 19]. Feasibility thresholds for assessing the study’s ability to inform a future randomised controlled trial, according to the primary outcome measures, are listed in Table 3. Thresholds were incorporated into traffic light criteria with SMG and expert PPI consensus. Where appropriate, thresholds are defined as proportions or percentages of participants so that all four outcomes can be evaluated together. In order to progress to a full trial without substantial changes in design, the trial must meet all the pre-specified quantitative thresholds with a 10% margin.

**Table 3 Tab3:** Summary of thresholds of feasibility to assess study design according to the study’s primary outcome measures

	GREEN—Study design feasible without changes	AMBER—Study design feasible with minor changes	RED—Study design not feasible without substantial changes
Recruitment	Able to recruit 30 patients in each arm in one year at single site Able to recruit ≥ 70% of approached patients	Able to recruit ≥ 50% of approached patients	Unable to recruit minimum threshold in single site in one year Unable to enrol 50% of approached patients
Adherence	At least 80% of patients remain in treatment allocation after randomisation,	At least 70% of patients remain in treatment allocation after randomisation	> 25% patients randomised to not receive OCS go on to receive them prior to day 2 visit
Timeliness	Patients enrolled in trial have obtained OCS (or a decision regarding OCS) within the same timeframe as patients of same severity in local site Patients enrolled in trial have same length of stay in the department compared to children of the same severity in local site	Patients enrolled in trial have a delay > 45 min (mean) in obtaining OCS (or a decision regarding OCS) Patient stay is not significantly extended, i.e. greater than hour due to study involvement	Patients enrolled in trial have a delay > 60 min (mean) in obtaining OCS (or a decision regarding OCS) Patient stay is significantly extended by enrolment in trial
Acceptability	> 70% parents agree or strongly agree that the interventions are acceptable on survey responses Global assessment demonstrates that parents feel that the benefits of participation outweighs the burden of the trial	> 50% parents agree or strongly agree that the interventions are acceptable on survey responses Parents feel that some of the benefits of participation outweighs the burden of the trial, but other components may be too demanding	> 30% parents disagree or strongly disagree that the interventions are acceptable on survey responses Global assessment demonstrates that parents feel that the burden of the trial outweighs the benefits of participation

Quantitative secondary outcome analysis will also be descriptive. The proportion of patients undergoing second NS and finger prick blood tests will be reported, and the viral pathogens detected on all point-of-care testing will be described along with CT values of positive tests. The proportion of discordant viral swab results between consecutive tests in the same patient will be reported. The study has been designed to minimise missing data for the primary analysis; missing data will be excluded from the analyses.

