## Intervention

Oral corticosteroid is usually given in the RBHSC ED as oral dexamethasone (typically 0.3 mg/kg). It is given as a single dose; therefore, adherence is not an issue in the acute setting. If the participant vomits within 30 min of dexamethasone administration, it may be re-administered at the discretion of the treating clinician and recorded in the CRF. The unblinded clinician may choose to determine the OCS therapy plan at any point after enrolment, irrespective of allocation (e.g. prescribe OCS to a child randomised not to receive OCS). Any deviation from planned study randomisation will be recorded on the CRF. After randomisation, participants will continue to follow this RBHSC guideline; there will be no further difference in-between arms. Clinicians may perform investigations and administer additional treatment according to local hospital guidance. These, and any other concomitant medications, will be recorded on the CRF.

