## Sample size and recruitment

The PRECISE study will recruit a minimum of 30 participants testing positive for RSV and 30 participants testing negative for RSV. However, as RSV status will be determined after enrolment, the PRECISE Study has the capacity to enrol up to 150 participants to ensure minimum requirements are met.

A target of 30 participants per group is in line with literature for feasibility studies using mixed methodology [18–20]. In order to truly address the primary outcome of acceptability in this feasibility study, it is imperative that the voice of families is represented. A minimum of 60 participants was informed by an anticipated attrition rate to complete surveys (50%) and uptake of qualitative interviews (15%) from previous studies [21]. This needs to be achieved in both treatment arms to ensure that adherence is not different depending on viral status. Feasibility of achieving this target is supported by local audit data of ED attendances in previous winter seasons.

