## Safety, ethics and governance

Recording adverse events associated with OCS use such as rash/allergic reaction, vomiting, or behaviour change, represents standard care. Any adverse events reported as part of routine clinical care will be summarised and reported.

The PRECISE Study protocol [Protocol V3 18/11/2024] has received a favourable opinion from the Health and Social Care Research Ethics Committee A [Reference 24/NI/0050]. The investigators will conduct the study in compliance with the protocol that was given approval/favourable opinion by the REC. Any protocol deviations will be documented and escalated as appropriate. Of note, the open-label nature of this study is such that the final decision for delivery (or not) of OCS is at the discretion of the treating clinician. Indeed, adherence to the treatment arm is an outcome measure of feasibility, and non-adherence to the treatment arm is not considered a breach of protocol compliance. Patient confidentiality and data protection are held with utmost importance, and as described, data management and sample handling will comply with necessary regulations.

The Study Management Group (SMG) is comprised of the PI, study co-ordinator, an independent advisor from the Northern Ireland Clinical Trials Unit (CTU), and three other co-investigators who provide study-specific expertise. The SMG meets at least quarterly by teleconference and will communicate between times via email as needed. Meetings will be formally minuted and stored in the SMF. As described above, regular data review will be carried out by the study co-ordinator and available for audit by the Belfast Trust and sponsor.

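### Table 3's Adherence bands measure different things, so on the printed thresholds a result can be Green and Red at once or fit no band, and no precedence rule settles it

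*Protocol article*

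**What the plan says.** All references are to the Protocol article.

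- **Green** (Table 3, Adherence row): "At least 80% of patients remain in treatment allocation after randomisation".
- **Amber** (same row): "At least 70% of patients remain in treatment allocation after randomisation".
- **Red** (same row): more than 25% of "patients randomised to not receive OCS go on to receive them prior to day 2 visit".
- **Denominator** (Data analysis and criterion for assessing feasibility of trial): "The proportion of enrolled patients remaining in their allocated treatment arm will be described as percentages of the total number randomised". The primary outcome list also defines adherence over enrolled patients, without splitting by arm.
- **Progression** (same section): to go forward without substantial design changes, "the trial must meet all the pre-specified quantitative thresholds with a 10% margin". The direction and scale of the margin are not given.
- **Clinician override** (Intervention): "The unblinded clinician may choose to determine the OCS therapy plan at any point after enrolment, irrespective of allocation". Safety, ethics and governance adds that "the final decision for delivery (or not) of OCS is at the discretion of the treating clinician", so a departure from allocation can go either way.
- **Timing of adherence review** (Table 2): at the ED attendance, at the 2-working-day visit and at 28 days.

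**The concern.** The three bands should cut one scale into three pieces, and they do not. Moving from Amber to Red changes three things: the event counted (any departure from allocation becomes crossover into OCS only), the denominator (all randomised becomes the no-OCS arm) and the window (open-ended becomes before the day 2 visit). A no-OCS child given OCS on day 10, for instance, could count against Green and Amber but never towards Red.

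Bands built on different quantities can overlap and can leave gaps, and the table has no tie-break. Adherence is a primary outcome and one of the four criteria that decide whether the definitive trial can go ahead as designed. If the result lands in an overlap or a gap, an unblinded team has to choose the label after seeing the data.

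**Working it through.** The article derives no figure for these thresholds, so there is none to reproduce. The check is a count of outcomes.

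**Inputs.** The minimum is 60 children (30 RSV-positive, 30 RSV-negative; Sample size and recruitment), allocated 1:1. I take exactly 30 per treatment arm, which is also the per-arm number in the Recruitment row of Table 3. Let X be the OCS-arm children not given OCS and Y the no-OCS children given OCS. Amber is read as 70% to under 80%.

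**Bands as printed**
- Green: (60 − X − Y)/60 ≥ 0.80, so X + Y ≤ 12.
- Amber: (60 − X − Y)/60 ≥ 0.70 and not Green, so 13 ≤ X + Y ≤ 18.
- Red: Y/30 > 0.25, so Y > 7.5, that is Y ≥ 8.

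**Overlap.** With X = 0, Y = 8 gives 52/60 = 86.7% and Y = 12 gives 48/60 = 80.0%. Every count from 8 to 12 (26.7% to 40% crossover) is Green and Red. The overlap narrows as X rises: 8 to 11 at X = 1, only 8 at X = 4, none from X = 5. At the maximum sample (75 per arm) it is Y = 19 to 30.

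**Gap.** No band applies when X + Y ≥ 19 and Y ≤ 7. With Y = 0 this is X = 19 to 30, pooled 41/60 = 68.3% down to 30/60 = 50%. With Y = 7 it starts at X = 12.

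**All 31 × 31 = 961 outcomes**

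| Classification | Outcomes |
|---|---|
| Green only | 76 |
| Amber only | 48 |
| Red only | 647 |
| Green and Red | 15 |
| Amber and Red | 51 |
| No band | 124 |

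These count possible outcomes. They are not probabilities.

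**Effect of the 10% margin on the overlap** (X = 0, margin applied to Green only)

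| Reading | Green cut-off | Departures allowed of 60 | Green and Red |
|---|---|---|---|
| Stricter, 10 points | 90% (54/60) | 6 | none |
| Stricter, relative | 88% (52.8, so 53/60) | 7 | none |
| As printed | 80% (48/60) | 12 | Y = 8 to 12 |
| Tolerance, relative | 72% (43.2, so 44/60) | 16 | Y = 8 to 16 |
| Tolerance, 10 points | 70% (42/60) | 18 | Y = 8 to 18 |

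**Mirror-image failures.** Using independent binomials with assumed rates, 30% non-receipt with 5% crossover is Green without Red with probability 77%. With 5% non-receipt and 30% crossover it is 28%. Both leave the same contrast in OCS receipt (70% − 5% = 95% − 30% = 65 points). With Green at 88% the two probabilities are both 14%, and at 90% both 7%, so this difference also depends on the margin.

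**The case against.** **The progression rule settles it.** Largely true. A Red result, or one that fails both Green and Amber, does not meet every threshold. A reader might infer that a Green-and-Red result could carry the trial forward unchanged. The text does not support that, because meeting all thresholds would probably block it. What stands is that Table 3 gives contradictory or missing labels, and that the blocking rule itself rests on an undefined margin.

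**The overlap may not exist.** Correct if the margin tightens Green to 88% or 90%. The table prints 80%, however, and nothing says which way the margin runs.

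**Green and Amber might be meant per arm.** The outcome definition and the analysis text both point to a pooled figure. Even per arm, Amber would allow 9/30 crossovers and Red would start at 8/30, so 8 and 9 would still conflict.

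**Heavy non-receipt is remote.** Fair. OCS is a single dose given in the ED, the Intervention section does not expect adherence problems there, and its only example of override is OCS given to a no-OCS child. A reader might infer that the lack of an arm-specific limit on non-receipt is itself an error. It is not: a stop on crossover, with non-receipt capped through the pooled figure, is a defensible choice by the study management group. The residual fact is that pooled Green, as printed and with no crossover, tolerates up to 12/30 OCS-arm children untreated.

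**Viral status.** A reader might take "This needs to be achieved in both treatment arms to ensure that adherence is not different depending on viral status" (Sample size and recruitment) as a requirement that Table 3 fails to test. That sentence follows the survey and interview numbers and mainly concerns the minimum sample. It sets no adherence test by RSV result.

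**Conclusion.** The point holds as an internal inconsistency in a printed decision rule. The bands use different events, denominators and windows, no band takes precedence, and pooled adherence below 70% does not trigger Red. On the printed thresholds, at 30 per arm with a fully adherent OCS arm, 8 to 12 crossovers are both Green and Red. Results under 70% pooled with at most 7 crossovers have no label. The Green/Red overlap is conditional on the margin: absent at 88% or 90%, wider at 72% or 70%. The gap below 70% remains whichever way the margin moves Green.

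The practical harm is limited, because the rule that all thresholds be met would probably prevent wrongful progression. It is still worth correcting: adherence is a primary outcome, the thresholds are presented as fixed in advance, and the people who would resolve the ambiguity are unblinded. The counts assume exactly equal arms of 30, and the probabilities rest on assumed rates.

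**What to change.** Reword the Adherence row:

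- **Window:** before the day 2 visit, for all bands.
- **Red:** more than 25% of the no-OCS arm given OCS (the existing limit), or pooled adherence under 70%. Red overrides.
- **Green:** pooled at least 80% and not Red.
- **Amber:** pooled 70% to under 80% and not Red.
- **Margin:** state whether the 10% tightens or relaxes the thresholds, and whether it is relative or in percentage points.
- **Reporting:** give adherence by arm beside the pooled figure.

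Every one of the 961 outcomes then has exactly one band. The cost is small. With true adherence of 80% in each arm, P(Y ≥ 8) = 23.9% and P(Y ≥ 8 or X + Y ≥ 19) = 24.1%, so the chance of Red hardly moves. Departures from allocation are already recorded on the CRF.

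**Option for the study management group:** apply the same 25% limit to OCS-arm non-receipt, since both failures dilute the treatment contrast equally. At 80% true adherence per arm this raises the chance of Red from 24% to 42%. It also leaves a narrow Amber band: with X ≤ 7 and Y ≤ 7, pooled adherence is at least 46/60, so Amber is 46 to 47 of 60. The crossover limit should not be relaxed to 30% to widen Amber, because 8 or 9 crossovers, now Red, could then be plain Green.

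Date the change, agree it with the management group and the PPI members who set the thresholds, and make it before adherence is summarised by arm. Recruitment has run since November 2024 with an unblinded team, so a later change could look data-driven.

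### The Table 3 acceptability bands overlap and leave a gap, and the percentage they use rests on survey responders when half of families are expected not to respond

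*Protocol article*

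**What the plan says.** All references are to the protocol article.

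- **Bands** (Data analysis and criterion for assessing feasibility of trial, Table 3, Acceptability). The Green survey criterion is "> 70% parents agree or strongly agree that the interventions are acceptable on survey responses". The Amber criterion is "> 50% parents agree or strongly agree that the interventions are acceptable on survey responses". Red switches to the opposite response and requires more than 30% of "parents disagree or strongly disagree that the interventions are acceptable on survey responses". Each band also carries a qualitative statement weighing benefit against burden. No rule says which band prevails if two are met or what happens if none is.
- **Missing data** (same section, closing paragraph). The design is meant to keep missing data low for the primary analysis, and "missing data will be excluded from the analyses".
- **Expected response** (Sample size and recruitment): "A minimum of 60 participants was informed by an anticipated attrition rate to complete surveys (50%) and uptake of qualitative interviews (15%) from previous studies". The same section sets the recruitment floor: "The PRECISE study will recruit a minimum of 30 participants testing positive for RSV and 30 participants testing negative for RSV". Capacity is up to 150.
- **Role of the criterion.** Acceptability is one of four primary outcomes. Progression to a full trial without substantial redesign depends on meeting all the quantitative thresholds, with a 10% margin.

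**The concern.** Two separate weaknesses affect the same criterion.

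The first is internal to Table 3. Green and Amber are defined on the share agreeing, Red on the share disagreeing. These are different quantities, and without a precedence rule one survey result can earn two colours or none. The Amber/Red boundary separates a design needing minor changes from one needing substantial changes, which is the distinction the progression rule turns on. Parents, clinicians, outcome assessors and the statistician are all unblinded, so a choice of colour made after the data are in would be made with the results in view.

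The second is the denominator. If about half of families do not return the survey and are left out, the reported percentage describes the responding half. The band is nevertheless read as a statement about the trial's families, and the article stresses that family voice must be represented.

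**Working it through.** **1. The plan's own figure.** With 50% survey attrition, 30 completed surveys need 30 / (1 − 0.50) = 60 enrolled, which matches the stated minimum of 60. The target of 30 completed surveys is my assumption; the article does not state it. Forward check: 60 × 0.50 = 30 surveys, 15 per RSV group, and 60 × 0.15 = 9 interviews.

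**2. Overlap.** Let a, d and u be the percentages agreeing, disagreeing and neutral, with a + d + u = 100. Amber without Green is 50 < a ≤ 70; Red is d > 30. Both hold whenever a > 50 and d > 30, which is possible for any a strictly between 50 and 70.
- Example: a = 60, d = 35, u = 5 is Amber and Red.
- With 30 responders: 18 agree (60.0%), 11 disagree (36.7%), 1 neutral is Amber and Red.
- Of the 496 possible splits of 30 responders, 15 are both. This is a count of splits, not a probability.

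**3. No neutral option.** Then d = 100 − a, and a < 70 forces d > 30. Every result strictly between 50% and 70% agreement is both Amber and Red. With 30 responders, 16 to 20 agreeing leaves 14 to 10 disagreeing (46.7% to 33.3%), so all five results are double-coloured. Only 21 agreeing and 9 disagreeing (exactly 70% and 30%) is Amber alone.

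**4. Gap, if there is a neutral option.** No band applies when a ≤ 50 and d ≤ 30.
- Example: a = 45, d = 25, u = 30.
- With 30 responders: 14 agree (46.7%), 8 disagree (26.7%), 8 neutral has no band.
- Count: a from 0 to 15 and d from 0 to 9 gives 16 × 10 = 160 of the 496 splits.

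**5. Green and Red.** a > 70 forces d < 30, so at the printed cut-offs the survey criteria for Green and Red cannot both be met.

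**6. Non-response.** Take 60 enrolled and 30 responders. The smallest Green count is 22, because 21/30 is exactly 70%.
- Among responders: 22/30 = 73.3%, exact (Clopper–Pearson) 95% CI 54.1% to 87.7%.
- Over all 60, if no non-responder agrees: 22/60 = 36.7%. If all agree: (22 + 30)/60 = 86.7%.
- Tipping points: exceeding 70% of 60 needs 43 agreeing, so 43 − 22 = 21 of 30 non-responders (70%). Exceeding 50% needs 31, so 9 of 30 (30%).
- At 150 enrolled and 75 responders, the smallest Green is 53/75 = 70.7%, with bounds 53/150 = 35.3% to 128/150 = 85.3%.

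The bounds are always as wide as the non-response fraction, here 50 percentage points, so a larger sample does not narrow them.

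**7. Direction.** Assume 75% agreement among responders and 50% response. Overall agreement is 0.5 × 75 + 0.5 × q, where q is agreement among non-responders: q = 30 gives 52.5%, q = 60 gives 67.5%, q = 75 gives 75%, q = 90 gives 82.5%. Responder-only scoring overstates agreement only if q is below the responder rate.

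**The case against.** Several objections have weight.

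- **Scoring a survey on its responses is ordinary practice.** Intervals and sensitivity analyses for non-response are commonly left to a full protocol or analysis plan that is not shown here. That stands, so their absence from an article is not an error in itself. It does not reach the bands, whose cut-offs are printed as prespecified criteria and conflict as written.
- **The 50% is a planning figure, and non-response is worked against and reported.** The survey goes out at two time points and can be read aloud. Missed reviews trigger repeat calls and an email, and families receive a voucher. Completion of follow-up is a secondary outcome, and a log of decliners with reasons is kept. All true, so much of the raw material for the response rate is already planned. What is lacking is its link to the band.
- **Acceptability is mixed-method.** Each band has a qualitative limb, and interviews triangulate the surveys. But the qualitative limb is not given as a tie-break, and interviewees complete the survey first, so interviews say nothing about those who never answered.
- **The gap depends on a neutral option.** Correct, and the response options are not given. Without a neutral option the gap disappears, but the overlap then takes in nearly the whole of Amber. The bands fail either way.
- **The 10% margin.** Its direction is not stated. It may move a bar, but it does not rank Amber against Red, and it leaves the 50-point width of the bounds unchanged.

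A reader might infer that the criterion is biased towards Green: families who refuse the swab are excluded, and disengaged families may be harder to reach. The article does not say that non-responders are less favourable. Exclusion at entry concerns who is enrolled, not who answers among those enrolled. Dropping non-responders also raises the agree and disagree percentages alike relative to an all-enrolled denominator, so the arithmetic has no built-in direction.

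**Conclusion.** The Table 3 acceptability bands are neither mutually exclusive nor, if neutral answers are possible, exhaustive. This follows from the printed cut-offs alone. It affects Amber against Red, and results with no band; it does not touch Green at those cut-offs. It needs correcting because a stated decision rule cannot be applied as written.

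The second point is more limited. With the anticipated 50% attrition and missing data excluded, the criterion is exposed to non-response bias of unknown direction. A just-Green result of 22/30 is compatible with 37% to 87% agreement among 60 enrolled families, before sampling error. These figures assume one parent response per child, exactly half responding, and Table 3 thresholds without the 10% margin. The documents support a statement about uncertainty, not a claim that acceptability will be overstated.

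**What to change.** Before results are examined:

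1. Define the survey bands on one quantity, keeping the plan's own cut-offs: Green >70% agreeing, Amber >50% to 70%, Red ≤50%. Report the percentage disagreeing alongside.
2. If a disagreement criterion is kept, state that it takes precedence and choose its cut-off so that Amber survives. An override at >30% disagreeing would not do this on a scale without a neutral option, where it would leave only exactly 70% agreement as Amber.
3. Next to the band, report the survey response rate, the exact 95% CI among responders, and worst-case and best-case bounds over all randomised families, or the non-responder agreement at which the band would change.

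A rule that Green must survive a fixed pessimistic assumption is not advised. If non-responders were taken to agree at half the responder rate r, overall agreement at 50% response would be 0.5r + 0.25r = 0.75r, so Green would need r > 93.3%. With 30 responders, 28 gives (28 + 14)/60 = 70% and fails, so 29 of 30 would be required. That would replace the agreed threshold with a different one.

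The cost is a change of table wording and a few extra reported figures, with no new data collection. The downside is that a Green result will carry visible uncertainty.
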